### Sample size estimation

This trial was designed to evaluate the efficacy of group A compared with group B in terms of the incidence of POPF. In cases using PGA felt at the pancreaticojejunostomy in partial pancreatoduodenectomy with an MPD diameter of 3 mm or less, the incidence of POPF was 15.5% [18, 19]. The incidence of POPF was 26% in a previous report without PGA felt at the pancreaticojejunostomy in partial pancreatoduodenectomy with an MPD diameter of 3 mm or less [29]. When statistical analysis is performed for a significance level of α = 0.05 (two-sided) in a superiority design, 231 patients are calculated to be required per arm, with a power 100(1 – β) of more than 80%, under the assumption that a small number of patients may be deemed ineligible and may thus be excluded from the analysis. Furthermore, as approximately 10% of the patients are expected to be ineligible for surgery, the sample size was eventually increased to 514 patients (257 patients per arm). This sample size was calculated using software PASS 15.0.6.

In the evaluation of the secondary endpoints, a hypothesis test will be used for comparison between both groups, although formal power calculations for these analyses have not been performed.

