### Randomization

After confirmation of eligibility, including written informed consent, patients are randomized in a 1:1 allocation ratio to either group A (polyglycolic acid felt reinforcement) or group B (control), preoperatively. Central randomization and registration will be applied, using the Electronic Data Capture (EDC) system (Seoul National University, Medical Research Collaborating Center). After being assessed for eligibility at registration, patients will be centrally randomized to either group A or group B. To minimize background bias between the two groups, this study is stratified for institution and suturing method to approximate the pancreas and the jejunum (mattress or non-mattress). We use Pocock and Simon’s minimization method for random assignment and the Mersenne Twister for random number generation. See Fig. 1 for a flow diagram of the PLANET-PJ trial.

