### Statistical analysis plan

All statistical analyses will be performed using the full analysis set (FAS) under the intention-to-treat principle. The significance level of this test is 5% (two-sided) and the confidence coefficient is 0.95. The Wilcoxon rank-sum test will be used for comparison of continuous variables. The Fisher’s exact test will be used for comparison of categorical variables. Kaplan–Meier curves will be used to represent time-to-event variables, and hazard ratios and 95% confidence intervals will be estimated by the Cox proportional hazard model. *P* < 0.05 will be considered significant.

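### The 231 evaluable patients per arm fit a normal-approximation calculation; under the planned Fisher's exact test they give about 77% power, not more than 80%

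*Protocol article*

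**What the plan says.** The Sample size estimation section of the protocol article assumes a POPF incidence of 15.5% with felt. For control it states: "The incidence of POPF was 26% in a previous report without PGA felt", in patients with a duct of 3 mm or less. The test is set at a "significance level of α = 0.05 (two-sided) in a superiority design", and "231 patients are calculated to be required per arm" for power above 80%. The same sentence says this was calculated "under the assumption that a small number of patients may be deemed ineligible and may thus be excluded from the analysis". The next sentence adds about 10% for patients expected to be ineligible for surgery, giving 257 per arm and 514 in total. PASS 15.0.6 is named as the software, but no test is named.

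The Statistical analysis plan section says that Fisher's "exact test will be used for comparison of categorical variables", and that all analyses use the full analysis set under intention to treat. It names no separate test for the primary endpoint. The Endpoints section makes the incidence of POPF primary. That is a yes/no outcome, so on the article's own terms it is compared by Fisher's test.

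**The concern.** A power statement holds for one particular test. Fisher's exact test is conservative for two binomial samples of this size, so it needs more patients than a Z-test or an uncorrected chi-square for the same power. If 231 came from a Z-type formula while the analysis uses Fisher's test, the stated power belongs to a test the trial does not plan to run, and the chance of missing the assumed effect is higher than the article says.

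There is also a practical risk. Some results would be significant by chi-square and not by Fisher's test. If the mismatch is noticed only after unblinding, a change of test would look data-driven.

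A second, smaller problem is that the text presents 231 as already containing some allowance for ineligible patients and then adds a further 10%. A reader would count two reserves.

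**Working it through.** **Inputs.** From Sample size estimation: p1 = 0.155, p2 = 0.26, difference 0.105, two-sided α = 0.05, power 80%, 231 evaluable and 257 randomised per arm. From Randomization: 1:1 allocation. From Statistical analysis plan: Fisher's exact test.

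**Step 1: reproduce 231.**
- Unpooled Z: n = (z₀.₉₇₅ + z₀.₈₀)² × [p1(1−p1) + p2(1−p2)] / (p1−p2)² = (1.960 + 0.842)² × (0.130975 + 0.1924) / 0.011025 = 230.2, so **231**.
- Arcsine: n = 2(1.960 + 0.842)² / h², with h = 2·asin√0.26 − 2·asin√0.155. This gives 230.7, so also **231**.
- Pooled Z (Pearson chi-square): 232.96, so 233.
- Continuity-corrected, the usual approximation to Fisher's test: 252.

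The inflation also reproduces: 231 / 0.9 = 256.7, so 257 per arm and 514 in total.

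So 231 is what a normal-approximation formula returns, with only rounding up. It contains no reserve for ineligible patients; the only reserve is the step from 231 to 257.

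**Step 2: exact power.** All pairs of counts from Bin(n, 0.155) and Bin(n, 0.26) were enumerated, and the probabilities of pairs that each test rejects at two-sided 0.05 were summed.

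| Patients analysed per arm | Fisher | Pearson chi-square, uncorrected | Unpooled Z |
|---|---|---|---|
| 231 | 76.75% | 79.9% | 80.3% |
| 248 | 79.8% | 82.6% | 83.0% |
| 249 | 80.0% (79.999%) | 82.8% | 83.2% |
| 250 | 80.2% | 83.0% | 83.3% |
| 257 | 81.2% | 84.1% | 84.2% |

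At 231 per arm the type II error under Fisher's test is 100 − 76.75 = 23.25%, against the stated figure of under 20%. Power first exceeds 80% at 250 per arm, 19 more than planned. With the same 10% allowance that is 250 / 0.9 = 277.8, so 278 per arm and 556 in total, against 514.

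**Step 3: actual type I error at 231 per arm.** With a common rate of 20.75% (the mean of the two assumed rates), Fisher's test has size 3.85%, Pearson 4.98% and unpooled Z 5.13%. With a common rate of 26%, Pearson has 5.04%. Fisher's lower power is the price of a guaranteed level; the other two hold 5% only approximately.

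**Step 4: can the 10% reserve close the gap?** It does if at least 250 per arm are analysed and the effect is undiluted, that is, if no more than 7 of 257 (about 3%) are lost. If patients who turn out not to be suitable stay in the analysis, the effect may be diluted. As an illustration (an assumption, not in the article), let a share d of group A have the control rate, so that p1 becomes 0.155(1−d) + 0.26d. With all 257 per arm analysed, Fisher's power is:
- d = 5%: p1 = 0.16025, power 76.5%
- d = 10%: p1 = 0.1655, power 71.3%

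**The case against.** The strongest reply is that the analysis is by intention to treat on the full analysis set and 257 per arm are randomised. If all are analysed, Fisher's test has about 81.2% power and the claim is met. This is correct as an upper bound. A reader might infer from the 76.8% figure that the trial as a whole is underpowered; the documents do not establish that, because the article does not say how many of the expected 10% will leave the full analysis set. But the article ties its power claim to 231, not 257, and keeps the difference for patients it expects to be ineligible. Under Interventions, protocol treatment ends if the duct exceeds 3 mm at operation. Such patients either leave the analysis or may dilute the effect.

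A reader might also infer that the sponsor demonstrably used an unpooled Z-test. The article names the software but no test, and the arcsine formula gives 231 as well. What stands is that 231 is too small for Fisher's test, whichever formula was used.

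Third, Fisher's test is a legitimate choice because it guarantees the 5% level. That stands: the choice is not an error, and type I error is not at risk. The power statement simply has to match it.

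Fourth, the gap is small next to the uncertainty in the rates. With control at 26.5% instead of 26%, Fisher's power at 231 is 80.3%; at 30%, in line with the Background's figure of over 30% for soft pancreas with undilated ducts, it is 95.5%. This limits the severity. It does not make the statement right at the rates the article assumes.

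Last, the full protocol or analysis plan may name another primary test. The point therefore concerns two published statements that disagree, not an omission.

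**Conclusion.** The point holds. At the article's own rates and significance level, the only test it gives for a categorical outcome has about 76.8% power at 231 evaluable patients per arm, about 3 points short of 80%, and needs about 250 per arm to exceed it. Depending on how much of the 10% allowance is lost, Fisher's power lies between about 76.8% (231 analysed) and 81.2% (257 analysed, no dilution). It could be lower if patients are kept and the effect is diluted.

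This assumes 15.5% versus 26%, equal arms, Fisher's test for POPF and no cost from the single interim look. That look, with O'Brien–Fleming type boundaries, would take slightly more power and is not included.

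The allowance attributed to 231 is a secondary wording error: no such reserve is in the number. Severity is should-fix. The power claim is misstated, but validity and type I error are unaffected.

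**What to change.** Choose one of two routes and record it before unblinding.

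1. Keep Fisher's exact test for POPF and restate power as about 77% at 231 evaluable per arm, and at most about 81% if all 257 per arm are analysed without dilution.
2. Name a primary test that matches the sizing: the uncorrected Pearson chi-square (79.9% at 231, so about 80% and not more than 80%) or the unpooled Z-test (80.3%). Say that the 5% level is then approximate and not guaranteed.

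A test stratified by the allocation factors should not be adopted as a remedy without its own power calculation. Institution (31) by suturing method (2) makes up to 62 strata, or about 7 evaluable patients each (462 / 62 = 7.5), and power would depend on how strata and any continuity correction are handled.

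In either case, name the test behind the 231, delete the clause saying that figure already allows for ineligible patients, and leave the later 10% inflation as the only reserve.

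The cost is a few sentences in the sample size and analysis sections, with no extra patients. Keeping both Fisher's test and the claim of more than 80% power, with the 10% loss, would instead take about 556 patients, 42 more than planned.

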### Statistical analysis plan

All statistical analyses will be performed using the full analysis set (FAS) under the intention-to-treat principle. The significance level of this test is 5% (two-sided) and the confidence coefficient is 0.95. The Wilcoxon rank-sum test will be used for comparison of continuous variables. The Fisher’s exact test will be used for comparison of categorical variables. Kaplan–Meier curves will be used to represent time-to-event variables, and hazard ratios and 95% confidence intervals will be estimated by the Cox proportional hazard model. *P* < 0.05 will be considered significant.

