**Methods:**

Patients diagnosed with pancreatic or periampullary lesions in whom it is judged that the main pancreatic duct diameter was 3 mm or less on the left side of the portal vein without pancreatic parenchymal atrophy due to obstructive pancreatitis are considered eligible for inclusion. This study is designed as a multicentre randomized phase III trial in Japan and the Republic of Korea. Eligible patients will be centrally randomized to either group A (polyglycolic acid felt reinforcement) or group B (control). In total, 514 patients will be randomized in 31 high-volume centres in Japan and Republic of Korea. The primary endpoint is the incidence of POPF (International Study Group of Pancreatic Surgery grade B/C).

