## Discussion

Partial pancreatoduodenectomy is an advanced procedure requiring a high level of surgical technique. With the development of surgical techniques and perioperative management in recent years, surgical-related mortality rates have become less than 5%. Nevertheless, the incidence of complications remains high at 30–65% [1–10]. In particular, the high frequency of POPF is problematic, because the various complications according to POPF, including intraabdominal haemorrhage or intraabdominal abscess, can be fatal.

There is no evidence to prove a safe and reliable procedure of pancreaticojejunostomy. We planned this study to evaluate the efficacy of a new method using double-coated PGA reinforcement to prevent POPF after pancreaticojejunostomy. This trial is a multicentre randomized phase III trial in Japan and Republic of Korea that is the first international study in pancreatic surgery. This study is designed to evaluate the usefulness of group A (double coating of PGA felt) compared with group B (without PGA felt) in terms of the frequency of POPF as the primary endpoint. Upon randomization, the eligible subjects will be stratified by the institution and suturing method to approximate the pancreas and the jejunum (mattress or non-mattress). The reason is that these factors may affect the incidence of POPF. Therefore, we will set these two factors for allocation in this study for appropriate analysis and evaluation. Moreover, we randomize the patients preoperatively after evaluating appropriateness in the CT image just before surgery. It would be ideal to randomize during surgery after the measurement of the diameter of the main pancreatic duct, but this is very difficult because of the situation of the participating facilities in this study.

All patients are blinded to the surgical approach that they will be receiving, and they are required to sign an informed consent before enrolling in this study [24]. However, blinding of the surgeons is not possible, owing to the different techniques used during the operation. This can be a potential source of inevitable bias. The anastomotic drains will be placed in all enrolled patients because measurement of the amylase level in the anastomotic drains is required for assessment of POPF, although recent meta-analysis revealed that pancreatic resection with or without abdominal drainage results in similar rates of mortality, morbidity and reintervention [30].

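### The stated test for a binary outcome, unstratified Fisher, falls short of the stated power at 231 per arm and ignores both minimisation factors: a modest loss of efficiency, not of validity

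*Protocol article*

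**What the plan says.** The primary endpoint is binary: "The primary endpoint is the incidence of POPF (International Study Group of Pancreatic Surgery grade B/C" (Abstract, Methods).

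The Randomization section says that "this study is stratified for institution and suturing method to approximate the pancreas and the jejunum (mattress or non-mattress" and that the method is Pocock and Simon's minimisation. The Discussion explains that the two factors may affect POPF, and that "we will set these two factors for allocation in this study for appropriate analysis and evaluation".

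The Statistical analysis plan section gives one test for each type of variable. For categorical variables it is Fisher's test: "exact test will be used for comparison of categorical variables". For continuous variables it is the Wilcoxon rank-sum test. No stratified or adjusted comparison is described anywhere. POPF by suturing method appears under Endpoints as a secondary endpoint, which does not adjust the primary comparison.

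Sample size estimation sets "a significance level of α = 0.05 (two-sided) in a superiority design", "with a power 100(1 – β) of more than 80" per cent, at 231 patients per arm. It then raises this to 257 per arm because about 10% are expected to be ineligible for surgery. It does not name the test behind the calculation.

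**The concern.** Two things pull the stated test below its nominal level.

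- Fisher's exact test is conservative with binary data at this sample size, whatever the method of allocation.
- Minimisation on prognostic factors takes between-stratum variation out of the treatment difference. An unstratified test still counts that variation in its standard error.

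Both cost power. The protocol gives a reason to expect the second, since it chose the factors because they may matter for POPF and says they serve the analysis, yet the stated test makes no use of them. What is at stake is whether the trial has its stated power at its own planning number, and whether information already collected at allocation is put to use.

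**Working it through.** **Inputs.** From Sample size estimation: "the incidence of POPF was 15.5" per cent with felt; "The incidence of POPF was 26% in a previous report without PGA felt"; two-sided α = 0.05; 231 evaluable and 257 randomised per arm. From Study design: 31 institutions. The strength of the centre and suture effects is not given, so it is assumed over a range on the log-odds scale. No allowance is made for alpha spent at the interim analysis.

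**1. The plan's own figure.**

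- Unpooled normal approximation: n = (1.960 + 0.842)² × (0.26×0.74 + 0.155×0.845) / (0.26 − 0.155)² = 7.849 × 0.3234 / 0.01103 ≈ 230.2, so 231 per arm.
- Arcsine formula: 231. Pooled-variance formula: 233.
- Inflation: 231 / 0.90 = 256.7, so 257 per arm and 514 in total.

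The stated figures reproduce, but from a normal-approximation test. The continuity-corrected formula, which approximates Fisher's test, gives 252.

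**2. Power of the stated test**, by exact enumeration of the two binomials:

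| Evaluable per arm | Fisher power | Fisher size |
|---|---|---|
| 231 | 76.8% | 3.8% |
| 250 | 80.2% | 3.9% |
| 257 | 81.2% | 3.8% |

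**3. Splitting the loss.** Simulation at 462 patients, 31 unequal centres, two suturing methods, allocation nearly balanced within strata, 8,000 trials per setting. The Monte Carlo standard error of a power near 80% is √(0.8×0.2/8000) ≈ 0.4 points. CMH is the Cochran-Mantel-Haenszel test.

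| Centre SD / suture effect (assumed) | Fisher power | Chi-square power | CMH by institution, power | Fisher size | Chi-square size | CMH by institution, size |
|---|---|---|---|---|---|---|
| 0 / 0 | 77.2% | 80.6% | 80.3% | 3.6% | 4.5% | 4.4% |
| 0.5 / 0.5 | 76.8% | 79.8% | 80.7% | 3.3% | 4.2% | 4.6% |
| 0.8 / 0.5 | 77.6% | 80.9% | 83.1% | 2.9% | 4.0% | 5.0% |
| 1.0 / 0.7 | 78.6% | 81.7% | 85.0% | 2.4% | 3.2% | 4.6% |

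- Fisher to unstratified chi-square: 3.4, 3.0, 3.3 and 3.1 points. This is Fisher's own conservatism and hardly depends on the factors.
- Unstratified chi-square to CMH by institution: −0.3, 0.9, 2.2 and 3.3 points. This is the cost of ignoring the factors.

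**4. Minimisation as such.** Pocock-Simon minimisation balances the margins, not the institution-by-suture cells. A simulation of it at 462 patients (assumed biased coin 0.8, unequal centres, centre-specific suture preference; 3,000 trials per setting, standard error about 0.7 points) gave:

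| Centre SD / suture effect (assumed) | Fisher | Chi-square | CMH by institution | CMH by institution × suture |
|---|---|---|---|---|
| 0 / 0 | 78.0% | 80.5% | 79.7% | 77.6% |
| 0.5 / 0.5 | 77.9% | 80.1% | 80.6% | 78.7% |
| 0.7 / 0.6 | 77.2% | 79.4% | 80.4% | 79.8% |

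Full cross-classification loses information because the cells are sparse: 31 × 2 = 62 cells for 462 patients is about 7.5 patients each. With 231 × (0.155 + 0.26) ≈ 96 expected events, that is about 1.5 events per cell. With no prognostic effect, stratifying by institution costs 80.5 − 79.7 = 0.8 points against chi-square, and full cells cost 80.5 − 77.6 = 2.9 points.

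**The case against.** The best defence has four parts.

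- **Sample size.** The analysis set is the full analysis set under intention to treat. If all 257 per arm are analysed, Fisher's test reaches 81.2% and the stated power is met. This stands. The shortfall arises only if the expected 10% leave the analysis. But the protocol ties its power statement to 231 and itself expects that loss.
- **Cause.** A reader might infer that ignoring the allocation factors is the main fault. The figures do not support that. Most of the loss is Fisher's conservatism, which would be there under simple randomisation too. The part due to the factors can be zero, and the protocol says only that they may affect POPF.
- **Remedy.** A reader might infer that stratifying by every institution-by-suture cell is the natural cure. Under minimisation it does not clearly beat a plain chi-square test in any setting tried.
- **Condensed article.** The sentence on Fisher's test is generic, and an unseen analysis plan may contain an adjusted primary analysis. That is possible, and the Discussion's wording is compatible with it. Still, the article states a test rather than leaving it open, and that test is unstratified.

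A reader might also infer that the trial risks false positives. It does not: an unstratified test after balanced allocation errs on the conservative side. Nor is a large gain shown for drain duration or hospital stay. The protocol gives no centre variation for them, and its mention of Kaplan-Meier and Cox methods without naming endpoints leaves their test a matter of inference.

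**Conclusion.** The point holds as one of efficiency and calibration. At 231 per arm the stated test has 76.8% power where more than 80% is claimed, and it needs about 250 evaluable patients per arm to reach 80%. These figures rest only on the protocol's event rates and the full 5% level. Of the loss, about 3 points (2.2 to 3.4 across the two simulations) belong to Fisher's test. A further 0 to 3 points or so belong to ignoring the allocation factors. That second range rests on assumed centre and suture effects and on how closely minimisation balances the strata. Validity is not in question. The change is worth making because it is nearly free, not because the trial fails without it.

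**What to change.** Name a primary test for POPF that accounts for the allocation factors without very sparse cells. Either of these would do:

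- a Cochran-Mantel-Haenszel test stratified by institution, with small centres pooled within country by a size threshold set in advance; or
- a logistic model with suturing method as registered at allocation and institution (pooled, or as a random effect), followed by a standardised risk difference with 95% CI.

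Use the registered suturing method, because the Surgical procedure section allows the method to change during the operation. Keep Fisher's test as a sensitivity analysis. Settle the choice before the interim analysis, so that its boundary applies to the same statistic throughout. A stratified Wilcoxon (van Elteren) test for drain duration and hospital stay is an optional extension on the same reasoning; its gain has not been quantified.

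The cost is some wording and a little extra analysis; both factors are already recorded for allocation. If they turn out not to be prognostic, stratifying by institution loses at most about 1 point of power against a plain chi-square test. Full institution-by-suture cells would lose about 3, which is why they are not recommended.
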